#### Screening and diagnostic interview

The preliminary screening will collect demographic data from participants, including their age, gender, education, therapeutic experience, and medication use, and the PAS will be administered (for a detailed description see the section regarding the primary outcome measure)
[34, 35]. Item 9 of the BDI-II
[37, 38] will be used to screen for suicidality. The BDI-II is a 21-item assessment of depressive symptoms that has demonstrated high internal consistency using outpatient samples
[37].

The SCID-I
[39] will be used to assess the presence of PD, agoraphobia, other anxiety disorders, and current depressive episodes. A trained interviewer will perform the interview via telephone. Previous studies have demonstrated the validity of telephone-based SCID-I interviews
[41, 42].

### Primary outcome measure

#### Panic severity

The primary outcome will be the severity of panic and agoraphobia symptoms as assessed by the total PAS score
[34, 35, 48]. This questionnaire was originally developed as a self- and observer-rating scale. In this study, we will use the self-rating questionnaire that was adapted into an online version. The PAS consists of 13 items grouped into five subscales, and an extra item regarding unexpected versus expected panic attacks. The five subscales assess the following areas: panic attacks, agoraphobic avoidance, anticipatory anxiety, daily life limitations, and health concerns (for example, the fear of physical harm or the fear of an organic cause). These subscales can be evaluated separately or as a total score that combines all subscales, ranging from 0 to 52 points. A higher score on the PAS indicates more panic symptoms. The psychometric properties of the scale are satisfactory, with a Cronbach’s alpha of 0.86
[49]. A score of between 0 and 8 indicates no clinically relevant symptoms, scores of between 9 and 28 indicate moderate symptoms, and a score of 29 or higher indicates a severe level of symptoms
[49].

### Secondary outcome measures

#### Depression

Depressive symptoms will be measured using the Allgemeine Depressions-Skala (ADS)
[50], the German adaptation of the Center for Epidemiological Studies Depression Scale (CES-D)
[51]. The ADS consists of 20 items that refer to the previous week and are answered using a four-point Likert scale. The total score ranges from 0 to 60. Its internal consistency is α =0.89, and its split-half reliability is r =0.91
[50].

#### Quality of life

Quality of life will be measured using the EuroQol (EQ-5D)
[52] and the Short Form 12 (SF-12)
[53]. The EQ-5D is a well-established measurement of quality of life that consists of five items assessing mobility, self-care, common activities, pain and/or discomfort, and anxiety and/or depression, as well as a visual analogue scale concerning health status. We will also use the SF-12, which consists of 12 items that assess eight health domains: physical functioning, role limitations, pain, general health perception, vitality, mental health, emotional role, and social functioning. The SF-12 generates two summary scores: physical health and mental health.

#### Agoraphobic cognitions

Agoraphobic cognitions will be measured using the Agoraphobic Cognitions Questionnaire (ACQ)
[54, 55]. The ACQ consists of 14 items, and its total score ranges from 14 to 70. Craske *et al*. reported that the ACQ has an internal reliability of α =0.80
[56].

#### Bodily sensations

The Body Sensation Questionnaire (BSQ)
[54, 55] is a 17-item self-report questionnaire that measures bodily sensations. The BSQ ranges from 17 to 85 points and has a satisfactory internal reliability of α =0.87
[54].

#### Agoraphobic avoidance

The Mobility Inventory (MI)
[54, 55] measures agoraphobic avoidance. The MI consists of 27 items that address the most important agoraphobic situations. Each item is rated both for when patients are alone and when they are accompanied. These two scales have a summed score ranging from 27 to 135 points, respectively. The internal consistencies are α =0.94 (alone) and α =0.91 (accompanied)
[57].

#### Observer rating anxiety symptoms

In addition, the secondary outcome measures will include the observer-rated HAM-A
[43, 58] to obtain a more detailed understanding of symptom severity. The HAM-A is a 14-item clinician-reported rating scale with a total score ranging from 0 to 30. Thus, we will use the structured interview guide for the HAM-A (SIGH-A)
[59]. The interview has shown satisfactory inter-rater and test-retest reliabilities of Intraclass Correlation Coefficients of respectively 0.99 and 0.89
[59].

#### Economic evaluation

We will use an adaption of the Trimbos/iMTA questionnaire to measure the costs associated with psychiatric illness (TiC-P)
[60] with regard to the German healthcare system.

#### Diary data

EMA data will be collected via the mobile application GET.ON PANIC APP
[47]. This app contains a diary where clients can record their panic attacks and monitor their progress using daily summaries. With regard to the latter, clients will summarize their general anxiety levels, their degree of avoidance, and their moods each evening. The application also records the type and number of exposure exercises performed by the client.

#### Additional measures

We will also collect data concerning technology acceptance (via a questionnaire based on the technology acceptance model; TAM)
[61, 62], the usability of the smartphone app GET.ON PANIC APP (via the System Usability Scale; SUS)
[63, 64], user satisfaction of the online training (a self-designed questionnaire based on the German version of the Client Satisfaction Questionnaire
[65, 66], and the adverse effects of psychotherapy
[67].

### Statistical analyses

The analyses will be performed based on the Consolidated Standards of Reporting Trials (CONSORT) statement regarding eHealth
[68]. The data will be analyzed on an intention-to-treat basis. We will also conduct per protocol and completers-only investigations as secondary analyses.

#### Treatment efficacy

Group differences in the baseline values of the primary outcome will be compared using t-tests to assess whether randomization was successful. Missing data will be addressed following the recommendations of Little and Rubin
[69] and Schafer
[70]. We will analyze the PAS data at eight weeks post-treatment using between-group analyses of covariance with regard to the individual baseline PAS scores, adjusted for sex, age, and socioeconomic status. We will use Cohen’s d to measure the between-group effect size. Cohen’s d will be calculated as the difference between the mean post-test scores of the intervention group and the control group divided by the pooled standard deviation
[71]. All other secondary outcomes will be analyzed in a similar manner.

We will also conduct clinical significance change analyses as described by Jacobson and Truax
[72]. In the first step, we will test whether the changes from pre-test to post-test are statistically reliable and build a reliable change index (RCI). In the second step, we will calculate clinical significance. Based on the RCI, the participants who display a reliable positive change, no change, or a reliable deteriorated change will be classified as responders, non-responders, or deteriorated, respectively
[72]. We will use mixed-model regressions to examine the long-term effect on the primary outcome after three and six months.

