### Sample size

The sample size for this study is based on the meta-analysis of self-help treatments for anxiety disorders by Haug *et al*.
[13]. An effect size of d =0.83 was derived for PD after comparing the self-help group with the waitlist/placebo group. Because hybrid online training was not integrated into the meta-analysis, we chose a conservative estimation of d =0.60. To examine the efficacy of GET.ON PANIC with a two-tailed t-test (α =0.05; 1-β =0.80), a sample of 45 participants will be needed for each group. Thus, the total sample size for this study will be 90 participants.

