### Randomization

We will use the computer program DatInf RandList Version 1.2 (DatInf GmbH, Tübingen, Germany)
[40] to randomize participants into either the intervention group or the waitlist control condition. This random assignment will be stratified for clinical or subclinical symptomatology, as well as the presence or absence of agoraphobia.

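### Baseline t-tests cannot show whether randomization succeeded; separately, Cohen's d from raw post-test means lets chance baseline imbalance into the reported effect size

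*Protocol article*

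**What the plan says.** Under Treatment efficacy, the protocol article states that the two arms' PAS scores at baseline are to be "compared using t-tests to assess whether randomization was successful". It gives no significance level for this test and ties no action to its result.

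The same section fixes the primary analysis as an ANCOVA of the eight-week PAS on baseline PAS, also adjusted for sex, age and socioeconomic status. It then defines the between-group effect size, scaled by the pooled SD, without baseline adjustment: "Cohen’s d will be calculated as the difference between the mean post-test scores of the intervention group and the control group".

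Under Randomization, allocation is produced by a computer program. "This random assignment will be stratified for clinical or subclinical symptomatology", and also for the presence or absence of agoraphobia. Under Sample size, the planning effect is d = 0.60 and "a sample of 45 participants will be needed for each group".

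**The concern.** There are two separate points.

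**The inference from the t-test.** A t-test asks whether an observed difference is larger than chance would readily produce. If the allocation list was followed, chance is the only source of a baseline PAS difference, so the null hypothesis is true by design. Rejection is then a false alarm, and non-rejection says nothing about whether the imbalance is small enough to ignore. The trial would publish a verdict on its own randomization that the test cannot give.

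**The effect size.** The hypothesis test is baseline-adjusted but Cohen's d is not. A chance baseline difference that persists to week 8 therefore appears in d as if it were treatment effect, or masks part of that effect. At stake is the accuracy of the published effect size, not the validity of the primary test.

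**Working it through.** **Inputs.** From Sample size: 45 per arm, d = 0.60, two-sided alpha 0.05, power 0.80. Assumed, because not stated: two-sided alpha 0.05 for the baseline test; baseline-to-post PAS correlation r of 0.3, 0.5 or 0.7; equal SDs at the two times. Steps 2, 3 and 5 ignore stratification, which step 4 brings in.

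**1. The plan's own figure.** The exact noncentral t calculation gives power 0.795 with 44 per arm and 0.804 with 45. The stated 45 per arm reproduces.

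**2. What the baseline test can detect.**
- Standard error of a standardized difference: √(2/45) = 0.211.
- Smallest significant observed difference: t(0.975; 88) × 0.211 = 1.987 × 0.211 = 0.42 SD.
- False alarms in sound trials: 5%, by construction.
- Chance imbalance above 0.2 SD: P(|t| > 0.2/0.211 = 0.95) = 34.5%; passed as non-significant: 34.5% − 5% = 29.5%.
- Chance imbalance above 0.3 SD: P(|t| > 1.42) = 15.8%; passed: 15.8% − 5% = 10.8%.
- Chance imbalance above 0.4 SD: P(|t| > 1.90) = 6.1%; passed: 6.1% − 5% = 1.1%.
- Median absolute chance imbalance: t(0.75; 88) × 0.211 = 0.677 × 0.211 = 0.14 SD.

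**3. If allocation were truly faulty.** Power to flag a real shift, noncentral t with 45 per arm:

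| True shift (SD) | Power |
|---|---|
| 0.2 | 16% |
| 0.3 | 29% |
| 0.4 | 47% |
| 0.5 | 65% |

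**4. Effect of stratification.** The strata plausibly relate to PAS, so balancing them narrows the chance differences. If they explain a share R² of PAS variance, the cutoffs in step 2 are divided by √(1 − R²). The document gives no R²; as an assumed range:
- R² = 0.2: false alarms P(|t| > 1.987/0.894 = 2.22) = 2.9%; imbalances of 0.30 to 0.42 SD passed: 11.5% − 2.9% = 8.6%.
- R² = 0.5: false alarms P(|t| > 1.987/0.707 = 2.81) = 0.6%; passed: 4.7% − 0.6% = 4.1%.

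The 5% and 10.8% in step 2 are therefore upper figures.

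**5. Does the primary analysis suffer?** In 40,000 simulated null trials per correlation, ANCOVA type I error was 0.049 to 0.050 overall and 0.046 to 0.057 among trials that the baseline test flagged. It does not suffer.

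**6. Carry-over into raw d.** Expected shift = r × baseline imbalance:

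| Baseline imbalance | r = 0.3 | r = 0.5 | r = 0.7 |
|---|---|---|---|
| 0.14 SD (median) | 0.04 | 0.07 | 0.10 |
| 0.40 SD (rare) | 0.12 | 0.20 | 0.28 |

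For scale, the planned d is 0.60.

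**The case against.** **No planned analysis depends on the test.** The ANCOVA is fixed in advance, and no covariate choice, exclusion or reanalysis follows from the t-test. This stands: deleting the test changes no efficacy result.

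**The test and the effect size are unrelated.** A reader might infer that the t-test causes the shift in d, or that a pass is meant to justify using raw means. The document does not support either reading. It never links the two, and raw d carries the same imbalance with or without the test. That is why they are treated here as separate points.

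**The large shift is an edge case.** A reader might take a shift of 0.20, a third of the planned effect, as typical. It is not: imbalances between 0.40 and 0.42 SD occur in about 1% of sound trials. Shifts are also equally likely in either direction, so they add noise and not systematic bias. The median case, about 0.07, is the fair figure.

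**"Cannot answer" is too absolute.** PAS is measured before randomization, so a marked difference could point to subverted or badly executed allocation. The null is true by construction only if the list was followed. This stands in part: the test is not empty for that purpose, but the power in step 3 makes it a weak check, and a more direct one exists.

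**Stratification lowers the error rates.** Accepted, and shown in step 4.

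**Conclusion.** The inference about randomization is wrong as written. Where allocation followed the list, a significant result is a false alarm (at most about 5% of sound trials, fewer with stratification), and a non-significant one does not show balance (0.30 to 0.42 SD passes in up to about 11%). Where it did not, the test would miss many faults of practical size. These figures rest on 45 analysed per arm and an assumed alpha of 0.05.

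The definition of Cohen's d is a separate matter and a free improvement. Using raw means typically moves the reported effect by about 0.04 to 0.10 in either direction over assumed correlations of 0.3 to 0.7. Rarely, at 0.40 SD, it moves it by 0.12 to 0.28.

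The primary ANCOVA and the sample size are unaffected. Severity is minor.

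**What to change.** In Treatment efficacy:

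1. Delete the baseline t-test sentence together with its conclusion about randomization. Report baseline PAS and the other baseline variables by arm descriptively (means, SDs, counts).
2. Define the between-group effect size as the ANCOVA-adjusted post-test difference divided by the pooled SD. Report the raw d alongside if it is wanted for comparison with other studies.
3. If execution of the randomization is to be checked, compare the actual allocations with the generated list, stratum by stratum.

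The cost is two text edits, plus the list comparison if wanted. No new data, participants or change in sample size are needed, and the adjusted difference already comes out of the planned ANCOVA.

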**Table 2 Tab2:** **Overview of instruments per time of assessment**

Assessments	Screening	T0	T1	T2	T3
Sociodemographic data	**x**	**-**	**-**	**-**	**-**
Suicidality (Item 9, BDI-II)	**x**	**-**	**-**	**-**	**-**
Diagnosis (SCID-I, sections for anxiety disorders and current depressive episode)	**-**	**x**	**-**	**-**	
Panic and agoraphobia severity, self-rating (PAS)	**x**	**x**	**x**	**x**	**x**
Panic and agoraphobia severity, observer-rating (HAM-A)	**-**	**x**	**x**	**-**	**-**
Agoraphobic cognitions (ACQ)	**-**	**x**	**x**	**x**	**x**
Body sensations (BSQ)	**-**	**x**	**x**	**x**	**x**
Agoraphobic avoidance (MI)	**-**	**x**	**x**	**x**	**x**
Depressive symptoms (CES-D)	**-**	**x**	**x**	**x**	**x**
Quality of life (EQ-5D, SF-12)	**-**	**x**	**x**	**x**	**x**
Economic evaluations (TiC-P)	**-**	**x**	**-**	**-**	**x**
Negative effects of online health trainings	**-**	**-**	**(x)**	**(x)**	**(x)**
Attitudes towards seeking psychological help	**-**	**-**	**(x)**	**-**	**-**
User satisfactory	**-**	**-**	**(x)**	**-**	**-**
Technology acceptance of smartphone app	**-**	**-**	**(x)**	**-**	**-**
Usability of smartphone app (SUS)	**-**	**-**	**(x)**	**-**	**-**

T0 = Baseline, T1 = 8 weeks, T2 = 3 months, T4 = 6 months.

Assessments: x = intervention and control group, (x) = intervention group only.

ACQ, Agoraphobic cognitions questionnaire; BDI-II, Beck Depression Inventory II; BSQ, Body sensations questionnaire; CES-D, Center for epidemiological studies depression scale; EQ-5D, EuroQol; HAM-A, Hamilton anxiety scale; MI, Mobility inventory; PAS, Panic and agoraphobia scale; SCID-I, Structured clinical interview for DSM-IV Axis I Disorders; SF-12, Short form 12; SUS, System Usability Scale; TiC-P, Trimbos and the Institute of Medical Technology Assessment Cost Questionnaire for Psychiatry.

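### The PAS is read twice before randomisation but the primary ANCOVA adjusts only for the T0 reading: a small missed efficiency, not an error

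*Protocol article*

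**What the plan says.** - **Two readings.** In Table 2 the row "Panic and agoraphobia severity, self-rating (PAS" is marked at Screening, T0, T1, T2 and T3. The marks are unbracketed, which the footnote explains: "Assessments: x = intervention and control group". The section on screening and the diagnostic interview confirms that at screening demographic data are collected "and the PAS will be administered".
- **Everyone randomised has both.** Study population sets a PAS entry window of 9 to 28, and Procedure uses the screening questionnaire to judge eligibility. Study design places the baseline assessment before randomisation.
- **One reading is used.** Treatment efficacy states: "We will analyze the PAS data at eight weeks post-treatment using between-group analyses of covariance with regard to the individual baseline PAS scores", with further adjustment for sex, age and socioeconomic status. Table 2 labels T0 alone as baseline. The screening PAS has no stated role in the efficacy analysis.
- **Sample size.** The trial is sized "with a two-tailed t-test (α =0.05; 1-β =0.80"), where "we chose a conservative estimation of d =0.60", so that "a sample of 45 participants will be needed for each group".

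**The concern.** A single PAS reading carries measurement error and day-to-day variation, so it is an imperfect covariate for the same scale at week 8. A second pre-randomisation reading of the endpoint already exists. Adjusting for it leaves the treatment effect being estimated unchanged, introduces no bias, and may reduce the residual variance of the primary comparison. The article names the covariates of the primary model, so this is a choice the plan has fixed rather than a detail left open. Table 2 collects sociodemographic data only at screening, so that questionnaire already supplies other covariates to the same model. What is at stake is a little precision in a 90-participant trial; validity is not in question.

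**Working it through.** **1. The plan's sample size.** Normal approximation: n per arm = 2(1.960 + 0.842)²/0.60² = 43.6, so 44. The exact t calculation gives 79.5% power at 44 and 80.4% at 45 per arm. The stated 45 reproduces. It rests on an unadjusted t-test.

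**2. What T0 adjustment already buys.** Let r be the T0 to week 8 correlation; the residual variance factor is 1 − r². The protocol gives no r. At an assumed r = 0.5 the factor is 0.75, and power at d = 0.60 with 45 per arm is 90.1%.

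**3. Adding screening, equal correlations, entry window ignored.** Let rb be the screening to T0 correlation. If both readings predict week 8 equally well, the residual factor is 1 − 2r²/(1 + rb). At r = 0.5:
- rb = 0.6: 0.6875/0.75 = 0.917, a fall of 8.3%
- rb = 0.7: 0.7059/0.75 = 0.941, a fall of 5.9%; power 91.8%
- rb = 0.8: 0.7222/0.75 = 0.963, a fall of 3.7%

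**4. Unequal correlations, entry window ignored.** If screening correlates s with week 8, then R² = (r² + s² − 2·r·s·rb)/(1 − rb²). At r = 0.5, s = 0.4:
- rb = 0.6: R² = 0.17/0.64 = 0.2656, a fall of 2.1%
- rb = 0.7: R² = 0.13/0.51 = 0.2549, a fall of 0.7%
- rb = 0.8: R² = 0.09/0.36 = 0.25, no fall

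The gain vanishes exactly when s = r × rb (here 0.5 × 0.8 = 0.4).

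**5. Using the mean instead.** The mean of the two scores has R² = [(r + s)/2]²/[(1 + rb)/2]. At r = 0.5, s = 0.4:
- rb = 0.7: 0.2025/0.85 = 0.2382; residual 0.7618/0.75, a **rise** of 1.6% over T0 alone
- rb = 0.8: 0.2025/0.90 = 0.225; residual 0.775/0.75, a **rise** of 3.3%

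**6. Allowing for the entry window.** Trivariate normal scores were simulated and cases kept only if screening PAS fell in 9 to 28. The unselected mean/SD was assumed to be 18/9, 20/10 or 24/10; r, s and rb are the unselected values. Ranges run over those three populations. Entries are the change in residual variance relative to T0 alone.

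| r (T0), s (screening) | rb | Both as covariates | Mean only |
|---|---|---|---|
| 0.5, 0.5 | 0.6 | −3.3 to −4.0% | same |
| 0.5, 0.5 | 0.8 | −2.0 to −2.2% | same |
| 0.6, 0.6 | 0.6 | −5.8 to −6.9% | same |
| 0.6, 0.6 | 0.8 | −3.3 to −3.8% | same |
| 0.5, 0.4 | 0.6 | −0.8 to −1.0% | about +0.3% |
| 0.5, 0.4 | 0.8 | 0.0% | +2.7 to +2.8% |
| 0.6, 0.5 | 0.6 | −1.9 to −2.2% | −0.5 to −0.7% |
| 0.6, 0.5 | 0.8 | −0.1% | +3.0 to +3.2% |

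So the fall is about 2 to 7% with equal correlations and about 0 to 2% if screening predicts week 8 less well by 0.1. In participants: 90 × 0.07 = 6.3, so roughly 0 to 6. A stronger assumption (r = s = rb = 0.7) gives 8 to 9%.

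**7. Cost of the extra covariate.** With intercept, arm, T0 PAS, sex, age and socioeconomic status (counted as one term), and complete data, residual degrees of freedom are 90 − 6 = 84; a further covariate leaves 83. The cost is about 84/83 − 1 = 1.2% of variance.

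**The case against.** The strongest reply is that nothing here is wrong. ANCOVA on the last pre-randomisation value is conventional and valid. The 80% power figure comes from an unadjusted test, so the planned model probably has power in hand. That stands, and it limits the point to an optional improvement.

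The second reply is about size. Screening is the earlier reading and the one directly cut to 9 to 28, so it may well predict week 8 less well than T0; steps 4 and 6 show the gain can then be almost nothing. That also stands. The interval between screening and T0 is not given, and the quoted reliability ("with a Cronbach’s alpha of 0.86") is internal consistency, so it does not supply the screening to T0 correlation.

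The third reply is that the remedy can backfire. For averaging the two scores, this is right (steps 5 and 6). For a separate covariate it is not: that cannot raise the underlying residual variance and costs only the degree of freedom.

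A reader might infer more than the documents support:
- **That the screening score is wasted.** It decides eligibility, and nothing excludes it from the missing-data handling.
- **That the gain could reach 14%.** That needs r = 0.6 and rb = 0.6 with equal correlations and no entry window (0.55/0.64 = 0.859).
- **That the trial is underpowered or biased without the change.** Neither follows.
- **That the plural baseline scores in the model already mean both readings.** The plural is explained by many individuals, and Table 2 labels only T0 as baseline.

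**Conclusion.** The point holds as a minor efficiency remark. The two pre-randomisation readings, and the use of only T0 in the stated model, are clear from the article. The benefit is about 0 to 7% of residual variance (roughly 0 to 6 participants on 90), before a cost of about 1% for the degree of freedom. This rests on assumed unselected correlations of 0.5 to 0.6 between T0 and week 8 and 0.6 to 0.8 between the two pre-scores, on screening predicting week 8 equally well or 0.1 less well, and on normal scores cut to the entry window. None of these values is in the protocol. The net effect could be close to nil, and no trial conclusion is likely to turn on it.

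**What to change.** In Treatment efficacy, add the screening PAS as a separate second covariate alongside T0 PAS in the 8-week PAS ANCOVA, and do likewise in the three- and six-month PAS mixed models. Keep T0 PAS in the model in its own right; do not substitute the mean of the two scores.

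The cost is one degree of freedom and a sentence in the plan. No data, visits or participant burden are added. Trial status says recruitment was already under way, so the change needs a dated amendment made before outcomes are compared by arm. If the sponsor prefers to leave the published model as it is, the analysis remains valid.

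### The primary ANCOVA leaves out both randomization stratification factors; if they predict outcome beyond the listed covariates and the strata were balanced, the test is somewhat conservative

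*Protocol article*

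**What the plan says.** In the protocol article, the Randomization section states: "This random assignment will be stratified for clinical or subclinical symptomatology, as well as the presence or absence of agoraphobia". It names the randomization software but does not describe blocking or any other restriction within strata.

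The Treatment efficacy section specifies the primary analysis of the Panic and Agoraphobia Scale (PAS) at eight weeks as "between-group analyses of covariance with regard to the individual baseline PAS scores, adjusted for sex, age, and socioeconomic status". It says the secondary outcomes will be handled in the same way. For the three- and six-month follow-up of the primary outcome it names mixed-model regressions and lists no covariates for them.

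The Sample size section bases the trial on an unadjusted two-sided t-test. For the effect size it says "we chose a conservative estimation of d =0.60", and it concludes that "a sample of 45 participants will be needed for each group". No credit is taken for covariates or for stratification.

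**The concern.** The design singles out two variables as important enough to control at allocation. The analysis then names four covariates, three of them beyond the baseline score, and includes neither stratification factor. This is a stated list that does not match the randomization, not a detail left open for an analysis plan.

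The statistical issue is precision. Balancing a prognostic factor across arms lowers the true sampling variance of the treatment difference. If the model omits the factor, the variance it explains stays in the residual, and the reported standard error does not reflect the gain. Confidence intervals are then wider, and p-values larger, than the design warrants. With 90 participants, precision available at almost no cost is worth keeping.

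**Working it through.** **1. The plan's own figure.** Inputs from the Sample size section: d = 0.60, two-sided α = 0.05, power 0.80, equal arms. Power is taken from the noncentral t distribution with 2n − 2 degrees of freedom and noncentrality d × √(n/2).

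- n = 44 per arm: power 0.795.
- n = 45 per arm: noncentrality 0.60 × √22.5 = 2.846, power 0.804.

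The stated 45 per arm reproduces.

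**2. Quantities the documents do not give (assumptions).**

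- p: the share of residual variance in eight-week PAS that the two factors explain beyond baseline PAS, sex, age and socioeconomic status. Range 0 to 0.20.
- R²: the share of variance explained by the listed covariates. Either 0, or 0.25 (a baseline–outcome correlation of 0.5).
- Each listed covariate takes one degree of freedom. The residual degrees of freedom are therefore 84 without the factors and 82 with them.

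**3. Analytic effect of adding the factors.** The standard error without the factors, relative to that with them, is 1/√(1 − p). The noncentrality is 2.846/√(1 − R²) without the factors and 2.846/√[(1 − R²)(1 − p)] with them. For example, with R² = 0 and p = 0.10 it is 2.846/√0.90 = 3.000.

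| p | SE ratio | Power with factors, R² = 0 (without: 0.803) | Power with factors, R² = 0.25 (without: 0.901) |
|---|---|---|---|
| 0 | 1.000 | 0.803 | 0.901 |
| 0.02 | 1.010 | 0.811 | 0.907 |
| 0.05 | 1.026 | 0.823 | 0.915 |
| 0.10 | 1.054 | 0.842 | 0.928 |
| 0.20 | 1.118 | 0.882 | 0.953 |

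Gains at p = 0.10: 0.842 − 0.803 = 3.9 points and 0.928 − 0.901 = 2.7 points. At p = 0.20: 7.9 and 5.2 points.

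**4. Simulation.** N = 90, 6,000 runs per scenario. Assumptions: permuted blocks of 4 within strata, 70% clinical, 60% with agoraphobia, each factor correlated 0.4 with baseline PAS, no dropout. Results for a baseline–outcome correlation of 0.5:

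| p | Model SE vs empirical SE, factors omitted | Type I error, omitted | Power omitted vs included |
|---|---|---|---|
| 0 | 0.186 vs 0.187 | 0.056 | 0.884 vs 0.881 |
| 0.05 | 0.186 vs 0.181 | 0.048 | 0.903 vs 0.911 |
| 0.10 | 0.186 vs 0.180 | 0.042 | 0.895 vs 0.913 |
| 0.20 | 0.186 vs 0.175 | 0.036 | 0.903 vs 0.943 |

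The 0.056 at p = 0, where the model is correctly specified, shows the size of the simulation error. At p = 0.20 the model standard error exceeds the empirical one by 0.186/0.175 − 1 = 6%. That is below the analytic 12%, because the two ratios have different denominators and because baseline PAS is correlated with the factors here. Balance on the factors then does not fully balance what remains of them after adjustment for baseline.

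A second simulation (8,000 runs per scenario, also blocks of 4) came closer to the analytic limit. At p = 0.05, 0.10 and 0.20 the model standard error was about 2.5%, 5-7% and 11% too large, and type I error was 4.5%, 3.8% and 2.9%. The 12% is therefore an upper figure for p = 0.20.

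**The case against.** The strongest objection is that baseline PAS, already in the model, may carry most of what the strata would add. The Panic severity section says: "The five subscales assess the following areas: panic attacks, agoraphobic avoidance, anticipatory anxiety, daily life limitations, and health concerns". At p = 0 nothing is gained by adding the factors, and at p = 0.02 almost nothing (simulated power 0.886 without, 0.889 with). This stands, and it is why the range must start at zero. Full absorption is not assured, however. Entry is limited to PAS 9 to 28. The total pools five subscales, so equal totals can hide different agoraphobia status. The article also does not say which instrument defines the strata; if it is the diagnostic interview, they carry information from a source other than the self-rating.

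A second objection is that the conservatism needs balance within strata, and the article describes no blocking. This also stands. Blocks of 4 are an assumption, and without restricted allocation the ordinary standard error would not be systematically too large.

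A reader might infer that the standard error is definitely too large and that the benefit of stratification is thrown away. The documents do not support this. Both conditions are unquantified, and the simulations show that part of the benefit of balance is kept even when the factors are omitted. A reader might also infer that the trial is underpowered or its primary test invalid. Neither follows: the 80% was computed without any covariate, and the error is in the conservative direction.

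**Conclusion.** The mismatch between the randomization and the stated covariate list is real. It affects the eight-week primary ANCOVA and the secondary outcomes analysed in the same way. Its consequence is conditional and modest: a possible loss of efficiency, running from none at p = 0 to the figures shown for p = 0.20. The treatment estimate is not biased, type I error is not inflated, and the planned power stands.

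The size rests on the assumed p, the assumed R², balanced allocation within strata and no dropout. The documents fix none of these. No omission is shown for the three- and six-month mixed models, because the article lists no covariates for them and may leave that to a fuller plan. This is an inexpensive improvement worth making, not a threat to the trial's conclusions.

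**What to change.** In the Treatment efficacy section, add clinical/subclinical status and agoraphobia (yes/no), with the values recorded at randomization, as fixed factors in the eight-week ANCOVA and in the secondary-outcome models that follow it. Specify this before outcome data are analysed, so that the choice of covariates cannot depend on results. Using the same two factors in the follow-up mixed models is sensible for consistency.

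The cost is one line of analysis wording and 2 degrees of freedom. Both factors must already be recorded in order to randomize. If they turn out not to be prognostic, power is essentially unchanged.
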